## Abstract

**Introduction:**

The perinatal period — encompassing pregnancy and the first months after childbirth — is a time of increased psychological vulnerability. It is often associated with high levels of anxiety, stress and depression. Access to psychological support is frequently limited by stigma, geographical barriers, and a shortage of services. Digital health interventions offer promising solutions to overcome these obstacles.

**Methods:**

This study evaluates the acceptability, feasibility, and user experience of REA, a virtual coach based on Acceptance and Commitment Therapy (ACT), to promote psychological well−being and prevent postpartum depression (PPD). Fifty pregnant women (25–30 weeks of gestation) will be recruited. The 8−week intervention delivers psychoeducational content via text, audio, and video, and collects steps, sleep, and heart rate via smartwatches for triangulation with self−reported measures. User Experience (UX) and User Engagement (UE) will be assessed with the System Usability Scale (SUS), the User Engagement Scale–Short Form (UES−SF), the Italian Chatbot Usability Scale, version B (ITA BUS B), and the User Version of the Mobile Application Rating Scale (uMARS), alongside semi−structured interviews. Psychological outcomes will be assessed pre–post with the two Whooley Questions, the Center for Epidemiological Studies Depression Scale (CES−D), the Multidimensional Psychological Flexibility Inventory (MPFI), and the 12−Item Short Form Health Survey (SF−12).

**Expected results:**

The intervention is expected to demonstrate high levels of user satisfaction and engagement (SUS ≥ 68, UES-SF ≥ 3,5/5; ITA BUS B ≥ 44/55 (≈4,0/5); uMARS ≥ 4,0/5), resulting in improvements in psychological flexibility, perceived well-being, and overall quality of life, recognizing that preventive efficacy will be evaluated in subsequent studies with controlled designs and postpartum outcome measures.

**Discussion:**

REA represents a scalable and accessible tool to support perinatal mental health, offering an innovative approach to the early prevention of postpartum distress.

**Trial registration:**

This study was approved by the ethics committee of the APSS (Provincial Health Services Authority) under number 12090 (May 15, 2025).

## Introduction

1

### Overview

1.1

The current body of scientific literature highlights an increasing need for psychological support among the general population, particularly among vulnerable groups exposed to high stress levels (1, 2). One of these vulnerable periods is the perinatal period, which is characterized by profound physical, psychological and social changes for women. How women adapt to these changes significantly impacts their quality of life and psychological well-being. Research indicates that pregnant women often experience psychological symptoms, with anxiety, stress, and depression being the most commonly reported (3, 4).

Estimates of postpartum depression (PPD) vary depending on symptom severity: postpartum blues (“baby blues”) is a transient and self−limiting mood disturbance in the early postpartum period that affects 30–80% of new mothers (5, 6). It is distinct from PPD, which affects about 10–15% of mothers (7) and is characterized by longer duration and/or greater severity with functional impairment. One challenge in treating PPD is that many mothers hide their symptoms, which is why it is often called “smiling depression” (8). Compared with other forms of depression, PPD includes distinctive symptoms such as confusion, auditory hallucinations, and delusions (9). Confusion is one of the most common and persistent symptoms (10), especially in severe cases (5, 11).

Although education and support have been proposed as preventive measures (5), few concrete programs have been implemented to date. Prevention is crucial because symptoms appear soon after childbirth and can significantly impact a child’s development, especially the mother-child bond in the first three months (9, 10, 12, 13).

While evidence supporting the effectiveness of psychological interventions for pregnant women is growing (14–16), significant barriers to accessing such care persist. Geographic limitations, the scarcity of trained professionals, and the stigma surrounding mental health issues often prevent women from seeking and receiving adequate support. For example, a recent Italian study on perinatal mental health practices revealed that 80% of Mental Health Departments (MHDs) lack structured care pathways, and Mother-Baby Units, which are essential for managing severe maternal mental health disorders requiring hospitalization, are unavailable in the country (17).

The World Health Organization (WHO) advocates for mental health promotion strategies that emphasize inclusivity and scalability. In this context, digital technologies have emerged as promising tools to address psychological well-being, as they offer accessibility, flexibility, and the potential to reduce barriers such as stigma and limited service availability (18).

This study aligns with the WHO’s strategic framework by evaluating the acceptability and feasibility of a digital intervention aimed at promoting psychological well-being and preventing perinatal mental health issues and PPD. Specifically, the intervention leverages third-wave cognitive-behavioral techniques, such as those based on Acceptance and Commitment Therapy (ACT), which have demonstrated their suitability for low-intensity, e-health-delivered interventions (19, 20). ACT is based on the idea that trying to change or avoid thoughts, feelings, or memories is often unhelpful (21). People tend to become “fused” with these private experiences, treating them as if they were facts. This can lead them to focus on changing what is actually out of their control, which distracts them from their true values and goals. ACT encourages the acceptance of these experiences, helping people reconnect with what matters to them. We selected ACT as the theoretical and intervention framework for four reasons. First, ACT directly targets psychological flexibility—a proximal mechanism in our preventive aims—and is measured in this study via the MPFI (19–21, 26). Second, ACT’s acceptance- and values−based strategies are well suited to addressing intrusive or distressing perinatal thoughts without pathologizing their mere occurrence (19–21). Third, ACT modules are amenable to low−intensity, self−guided, digitally delivered formats, consistent with our e−health design (19, 20). Finally, while various psychological interventions show promise in the perinatal period (14–16), ACT offers a coherent process−based approach aligned with prevention and scalable delivery. In addition, digital prevention programs have shown feasibility in perinatal populations, supporting our implementation choice (18).

In the case of PPD, the intense stress and changes after childbirth can lead to unexpected and disturbing thoughts or feelings. While some fusion with thoughts may not be harmful, fusion with unfamiliar or distressing experiences, such as “I wish I did not have this baby”, can have serious consequences. If the mother avoids or believes these thoughts, she may feel guilty or disconnected from her baby. Even if someone is not fully fused with all their thoughts, they might still strongly believe what they see or hear. This becomes problematic when those perceptions are false, such as in hallucinations. In PPD, hallucinations and delusions, especially auditory ones, are not uncommon (9). In this protocol, the term perinatal is employed to denote the entire continuum from pregnancy to the initial months following childbirth, a period that is characterized by vulnerability but also by opportunities for prevention. The intervention, which is administered during pregnancy, aims to enhance psychological flexibility, stress regulation and perceived well-being, thereby reducing the proximal risk factors for postpartum distress. Within this framework, the ACT-based digital intervention offers psychoeducational content and experiential practices to support perinatal adaptation and contribute to the prevention of postpartum distress and depression.

In summary, there is a need for scalable solutions that support perinatal mental wellbeing and reduce barriers to access. In consideration of the ACT theoretical rationale and the WHO framework on mental health promotion, the REA protocol is hereby presented. The REA protocol is a virtual coach integrated into TreC Mamma that delivers an 8-week psychoeducational program during the perinatal period. In the ensuing sections, we delineate the objectives, methodologies, metrics and analyses employed to evaluate its acceptability, feasibility, usability and engagement, in addition to pre-post psychological changes.

### Theoretical model

1.2

The present study is positioned within the design and development cycle of the ORBIT model (Obesity-Related Behavioral Intervention Trials) (22). It involves the delivery of material based on a validated intervention in text, audio and video formats by a virtual coach (i.e. a digital assistant), identified as REA (the name “Rea” was chosen for the chatbot about the Greek goddess Rhea, daughter of Uranus and Gaia, who is venerated in mythology as the mother of the Olympian gods), implemented within the TreC Mamma application (app).

This intervention is positioned within the framework of behavior change interventions (23), which aim to enable women to acquire adaptive strategies for their psychological well-being.

In this context the term *intervention* is used to identify an application - the virtual coach - that periodically proposes, in a predefined (rule-based), structured and orderly manner, psychoeducational material in audio, text and video format, structured and reviewed by psychological professionals. The end user reads and manages this material autonomously; therefore, the virtual coach is used as a simple information transmission tool.

### Goal of the study and research questions

1.3

The intervention is designed to enhance the improvement of women’s psychological well-being by helping them manage stressful situations more effectively through modules based on ACT principles and to prevent postpartum distress. The study also envisages collecting and using data from wearable devices (smartwatches, CE-marked and GDPR compliant) for triangulation with objective parameters (such as sleep quality or physical activity level) to support the women’s self-reported data.

The primary objectives of this proof-of-concept study are (1) to explore the User Experience (UX) and User Engagement (UE) of women interacting with the TreC Mamma application and the virtual coach, REA and (2) to assess, through semi structured interviews, participants’ experience with both REA and the application, as well as their emotional responses throughout the intervention.

The secondary objectives are to assess psychological well-being before and after the intervention, to administer self-assessment questionnaires at the beginning and end of the psychoeducational program, and to analyze the data collected via wearable devices. It is important to emphasize that the data collected from smartwatches on steps, sleep and heart rate are objective indicators of behavior and physiological status, and are used to triangulate self-reports. This data has exploratory and non-causal value.

## Methods

2

### Design and setting

2.1

REA, the virtual coach developed within the TreC Mamma application, will interact with women for 8 weeks starting from week 25/30 of pregnancy, with one month between the end of session 6 and the beginning of session 7.

Specifically, there will be one psychoeducational session per week with integrated exercises. The woman can choose the day and time that best suits her needs to interact with REA.

At the beginning of the course, REA will administer the 4 self-report questionnaires, namely the two Whooley’s Questions (24), the Centre for Epidemiological Studies-Depression Scale (CES-D) (25), the Multidimensional Psychological Flexibility Inventory (MPFI) (26) and the 12-Item Short Form Survey (SF-12) (27) to establish the baseline level.

After the data collection phase, the intervention will be administered, and its contents will be presented in different formats (text, images, audio, and video tracks).

The questionnaires will be further administered at the end of the intervention to assess whether the women perceived a change in psychological well-being and quality of life. These data will then be triangulated with the parameters collected by the smartwatch.

Four questionnaires will be administered in order to assess usability: User Experience (UX) and User Engagement (UE). Usability and engagement measures include the User Engagement Scale Short-form (UES-SF) (28), the System Usability Scale (SUS) (29), the Italian version of the Chatbot Usability Scale (ITA BUS B) (30), and the User Mobile Application Rating Scale (uMARS) (31). The questionnaires are managed by a microservice within the TreC platform that complies with the requirements and regulations in terms of personal data protection.

After two months, women who have given consent will be undergoing a semistructured interview in order to investigate their experience in using REA and the TreC Mamma application, and to understand how the women felt during the process.

### Participants, eligibility criteria, and screening

2.2

The study’s target population includes all pregnant women between 25 and 30 weeks of gestation attending the Pregnancy Care Service of the APSS in Trentino. Midwives from the APSS hospital and territorial service were involved in the study to identify women potentially eligible to participate.

Inclusion criteria to participate in the study are as follows: (1) being pregnant, (2) being in a gestational state between the nineteenth and twenty-sixth week, (3) being ≥ 18 years of age, (4) having a smartphone with Internet access, being able to download the app and being able to use it, (5) being a resident of the Autonomous Province of Trento, (6) knowing and understanding the Italian language, and (7) negative Whooley questions.

The exclusion criteria are as follows (1) patients unable to provide informed consent (a prerequisite for participation in the study), (2) inadequate understanding of the Italian language, (3) possible depression, (4) suicidal tendencies, (5) already being in/being in a psychological/psychotherapeutic pathway at the time of recruitment, (6) substance addiction/being in recovery for less than one year, and (7) a clinical history of previous psychological distress.

Recruited women who meet the inclusion criteria and give their consent to participate in the study will be enrolled in the study. All women who freely decide to take part in the study will be asked to sign an informed consent at the time of enrolment. After careful explanation of the study, its aims, how the data will be collected, managed and processed, the level of involvement required and the duration of the research, as well as any confidentiality issues. The woman will also be informed of the possibility of leaving the study at any time she wishes, without this in any way compromising the quality of care or interfering with her course of treatment, and without giving any explanation. The informed and conscious consent of the subject involved must be provided freely, voluntarily and in writing together with the data processing authorization form, prior to participation in the study. The women will be provided with the smartwatch and will sign the user agreement. The women will also receive an information sheet regarding the processing of personal data during the study. Copies of the informed consent and privacy policy regarding the study will be issued to the woman and will be available in the App. **Figure 1** shows a flowchart of the research project procedure.

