### REA intervention

2.3

The virtual coach, REA, delivers an intervention based on ACT techniques, also inspired by Espen Klausen’s manual (32). The intervention is designed to promote quality of life and perceived psychological well-being while also aiming to prevent psychological distress and PPD in pregnant women through a psychoeducational approach. The module is self-administered and available on both the Android and iOS platforms. All the contents of the dialogues have been developed by a group of psychologists belonging to the Digital Health Research unit of the Fondazione Bruno Kessler (FBK) in Trento and psychologists belonging to the Istituto Pavoniano Artigianelli in Trento, with specific competences in the field of communication, in collaboration with an ACT expert psychologist/psychotherapist, starting from the Handbook (ACT) for the prevention of distress and PPD (32). The content was subsequently reviewed by a senior psychologist from the Operative Psychology Unit of Trento’s Azienda Provinciale per i Servizi Sanitari (APSS).

The intervention spans 8 weeks, with 6 weeks before and 2 weeks after delivery (see **Figure 2**). Each session lasts approximately 20 minutes.

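### Inclusion criterion (2) sets gestational age at weeks 19–26, while the abstract and the stated target population say 25–30 weeks

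*Protocol article*

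**What the plan says.** Gestational age appears in four places in the Protocol article.

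- Abstract, Methods: "Fifty pregnant women (25–30 weeks of gestation) will be recruited".
- Section 2.2, first paragraph, on the target population: "The study’s target population includes all pregnant women between 25 and 30 weeks of gestation". Midwives are to identify potentially eligible women from this group.
- Section 2.2, inclusion criterion (2), in the very next paragraph: "being in a gestational state between the nineteenth and twenty-sixth week".
- Section 2.1, on the virtual coach: it "will interact with women for 8 weeks starting from week 25/30 of pregnancy".

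Section 2.2 also says which of these decides entry: "Recruited women who meet the inclusion criteria and give their consent to participate in the study will be enrolled in the study". The list of criteria, including criterion (2), is therefore the operative rule.

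**The concern.** Two consecutive paragraphs of section 2.2 describe populations that overlap only at their edges. By the target population and the abstract, a woman at 28 weeks belongs in the study; by criterion (2) she is ineligible. For a woman at 21 weeks the position is reversed. Staff who follow the criterion and staff who follow the description of the population would enrol different women, and either could later be said to have departed from the protocol.

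What is at stake is who enters the study and to whom its results apply. In a single-arm proof-of-concept study with 50 women planned, the description of the sample carries much of the weight. A report describing women at 25–30 weeks would be wrong if enrolment had followed criterion (2), and the reverse also holds.

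**Working it through.** The plan gives no figure to reproduce here. The check compares the windows as sets of weeks and then asks which event each place describes.

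**Inputs**

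- Criterion (2), section 2.2: 19th to 26th week.
- Target population, section 2.2, and recruitment, abstract: 25 to 30 weeks.
- Rule for enrolment, section 2.2: women who meet the inclusion criteria and consent.

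**Step 1: both windows read as week numbers**

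- Criterion (2): {19, 20, 21, 22, 23, 24, 25, 26}, 8 weeks.
- Target population: {25, 26, 27, 28, 29, 30}, 6 weeks.
- Shared: {25, 26}, 2 weeks. This is 2/8 = 25% of the weeks the criterion admits and 2/6 = 33% of the weeks in the target population.
- Admitted by the criterion but outside the target population: weeks 19–24, 6 weeks.
- In the target population but excluded by the criterion: weeks 27–30, 4 weeks.

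**Step 2: the criterion read as ordinal weeks**

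The criterion is worded with ordinals. If the 19th to 26th week means completed weeks 18 to 25, the only shared week is 25: 1/8 = 12.5% of the criterion's weeks and 1/6 = 17% of the target weeks. The conflict is then somewhat larger.

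These are shares of weeks, not of women. The documents do not say how eligible women are spread over gestational age, so they do not allow an estimate of how many women would be misclassified.

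**Step 3: which event each place describes**

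- The abstract speaks of recruitment.
- The target population is the group from which potentially eligible women are identified.
- Criterion (2) decides enrolment.
- Section 2.1 dates the start of the coach's interaction with the woman, which is a different event.

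The first three all concern entry to the study, and they disagree. Section 2.1 does not by itself contradict criterion (2), because a woman could consent earlier and begin the course at 25–30 weeks. The conflict is therefore between criterion (2) on one side and the abstract and target population on the other.

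**The case against.** The strongest defence is that two events are meant: consent at weeks 19–26 and a first session at weeks 25–30. That fits section 2.1, and the baseline questionnaires are given when the course begins, so such a lag would do no harm to them. What stands is that section 2.1 cannot be counted as a conflicting statement. The defence still does not settle the matter. No text shown states an interval between enrolment and the first session, the abstract attaches 25–30 weeks to recruitment, and section 2.2 attaches it to the population being approached. Figure 1 (procedure) and Figure 2 (chronology) are not shown and might label the steps, so the claim is limited to the text.

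It is also fair to say that both windows can be met together, at weeks 25–26, and that recruitment runs within one provincial service, so a forecast that sites would diverge is conjecture.

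A reader might infer further harms that the documents do not support.

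- **Timing of the later sessions.** Taking entry as the first session, adding six weekly sessions and then about four weeks for the gap ("with one month between the end of session 6 and the beginning of session 7"), session 7 would start at 19 + 6 + 4 = 29 to 26 + 6 + 4 = 36 weeks. That sits badly with section 2.3 ("The intervention spans 8 weeks, with 6 weeks before and 2 weeks after delivery"). But section 2.1 places the start at 25–30 weeks, so nothing supports sessions beginning at weeks 19–24, and any comparison with delivery needs an assumed delivery week that the documents do not give. Entry at 25–30 weeks gives 35 to 40 by the same sum, so the tension with sessions after delivery would remain for most entries under either window. It is a separate question.
- **Baseline and post-intervention assessments.** These follow the course, not enrolment, so criterion (2) does not fix their gestational age.
- **The covariate in section 2.7.1.** Section 2.5 collects the expected delivery date at enrolment, so gestational age at enrolment can be calculated under either window. There is no need to replace it.

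**Conclusion.** The concern holds as an internal inconsistency in the entry criteria. Criterion (2) governs enrolment, and it contradicts the population stated in the same section and in the abstract. The windows share weeks 25–26, or week 25 alone if the criterion is read in ordinal weeks. Taken literally as week numbers, the criterion lets in women at 19–24 weeks and shuts out women at 27–30 weeks.

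This rests on the text as shown and on no assumption about when sessions start or when delivery occurs. The sample size figures in section 2.6 are not affected.

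A reader might also infer that criterion (2) is simply the mistake, because 25–30 weeks appears more often. The documents do not support that. One of those appearances, in section 2.1, concerns the start of the course, and counting mentions does not show which window was intended or approved.

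The point should still be settled before enrolment relies on the text, because it decides who is eligible and whom the results describe.

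**What to change.** Check the abstract, the target population paragraph and criterion (2) against the ethics-approved text, and state one enrolment window in all three. If two events are intended, say so: label one window as gestational age at consent and the other as gestational age at the first session, and make the abstract and target population refer to the right one. State whether the limits are completed weeks or ordinal weeks, since that alone moves the criterion by one week. Confirm that Figures 1 and 2 agree with the result.

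If the approved text is already consistent, the cost is a wording correction to the article. If it carries the same conflict, a minor amendment is needed. If enrolment has already begun, report the window actually applied and the gestational age at enrolment of the women entered. No change to the sample size or to the covariates follows from this point.
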